### Trial monitoring

The chairman of the Department of Physiotherapy & Rehabilitation at Jashore University of Science & Technology will act as the coordinator of the trial monitoring team, assisted by two other volunteers from the Master of Physiotherapy program who are not involved in any aspect of this trial.

### Safety measures and managing adverse effects

All procedures will be carried out under the supervision of the trial monitoring team and a qualified physician with expertise in managing diabetic peripheral neuropathy (DPSN) in order to ensure the participants’ safety.

Manageable adverse events: Temporary increase in pain or tingling sensation and mild muscle soreness or fatigue**.**Serious adverse events: Considered fatal are severe nerve injury leading to permanent loss of sensation or motor function, diabetic foot ulceration, or any intervention-related complications resulting in infection or vascular compromise**.**

In addition to taking appropriate clinical measures, such as changing or stopping the intervention if needed, any adverse incidents will be documented and submitted to the ethics committee.

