**Methods:**

An assessor and patient-blinded randomized clinical trial (RCT) on 90 DPSN cases through hospital-based simple random sampling. Participants will be randomly assigned equally to either the Neurodynamic approach or the Sham neurodynamic approach group by concealed allocation between April and August 2025 at the Nurul Islam Diabetic Center in Jashore, Bangladesh. The experimental group will receive the Neurodynamic approach, and the control group will receive the sham approach; however, both groups will receive transcutaneous electrical nerve stimulation (TENS) and home exercises for 12 sessions over 4 weeks. A pretest will be taken at baseline, a posttest after 4 weeks, and a follow-up evaluation after 12 weeks. In addition to outcome measures, manageable and fatal adverse events will be documented and reported.

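### The plan labels survivable serious adverse events 'fatal', and its two event classes leave some unrelated serious events without a class

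*Protocol article*

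**What the plan says.** The section on safety measures and managing adverse effects in the protocol article names two classes.

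- **Manageable:** "Temporary increase in pain or tingling sensation and mild muscle soreness or fatigue".
- **Serious:** "Serious adverse events: Considered fatal are severe nerve injury leading to permanent loss of sensation or motor function, diabetic foot ulceration". The list closes with one further item: "any intervention-related complications resulting in infection or vascular compromise".

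The same section ends with a rule that applies to every event, whatever its class: "any adverse incidents will be documented and submitted to the ethics committee".

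The abstract, under Methods, gives the reporting scheme: "manageable and fatal adverse events will be documented and reported". There the word 'serious' does not appear; 'fatal' stands in its place.

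The Data analysis section specifies no safety table, no safety endpoint and no comparison of event rates between the groups.

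**The concern.** Seriousness, severity, relatedness and fatality are four different attributes of an adverse event, and the text merges three of them. It equates serious with fatal, although every harm it lists can be survived. It also makes relatedness a condition of seriousness for some harms and not for others.

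Two consequences follow for anyone coding events by this text. First, a non-fatal ulcer or nerve injury carries the label 'fatal', the label a reader would expect to mean death. Second, a serious event that is neither on the list nor caused by the intervention has no class to go into.

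This matters more here than in many trials of this size. The Introduction attributes 80% of diabetes-related foot ulcers to the condition under study and describes these patients as more prone to falls and injuries. The Discussion suggests that the intervention might lower the risk of falls and ulcers. Ulcers are therefore a foreseeable event and one on which readers may look for evidence, so they should be labelled for what they are.

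**Working it through.** No arithmetic applies. The article gives no event rates and no safety figure to reproduce. The check is to set the safety section beside the abstract and ask where particular events would go.

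**Inputs.** The manageable list, the serious list and the rule on documenting all incidents come from the safety section. The reporting classes come from the abstract's Methods.

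| Event | On the manageable list? | On the serious list? | Label under the abstract's scheme |
|---|---|---|---|
| Short-lived tingling after a session | Yes | No | Manageable |
| New foot ulcer, patient recovers | No | Yes, no relatedness condition | Fatal |
| Lasting nerve deficit from severe nerve injury | No | Yes, no relatedness condition | Fatal |
| Infection complicating the intervention, patient recovers | No | Yes | Fatal |
| Infection unrelated to the intervention | No | No | None |
| Vascular event unrelated to the intervention | No | No | None |
| Hospital admission for an unrelated cause | No | No | None |
| Death from an unrelated cause | No | Not named | Plausibly fatal, by the ordinary meaning of the word |

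**Step 1: labelling.** Rows 2 to 4 are survivable harms that receive the label 'fatal'. The article draws the distinction itself: its Introduction treats foot ulcers as something that can lead on to infection and death, not as deaths. Because 'fatal' appears both in the safety section and in the abstract, and replaces 'serious' altogether in the abstract, it functions as a category name and not as one stray word.

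**Step 2: mixing.** If the last row is placed under 'fatal' by ordinary meaning, that one class holds deaths together with ulcers in patients who survived. A count of the class would not give the number of deaths.

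**Step 3: coverage.** Rows 5 to 7 fall in neither class. For infection and vascular compromise the cause is the words limiting the item to intervention-related complications. Grammatically they attach only to that last item; nerve injury and ulceration carry no such limit. The admission has no class because hospitalisation is not a criterion.

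**Step 4: capture.** All eight events are still recorded, because the closing rule of the safety section covers any adverse incident. What rows 5 to 7 lack is a class, not a record.

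**The case against.** The strongest case on the other side is that this is a wording slip with little practical effect. The item is headed as serious adverse events and names its events, so a coder would probably understand that 'serious' was meant. Every incident goes to the ethics committee in any case. The article condenses a fuller protocol, where standard seriousness criteria and separate severity and relatedness fields may well appear.

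Much of that stands. No event is lost, and the absence of a complete list of seriousness criteria is the weaker part of the point, because a condensed article may leave it out. What does not fall away is the text that is printed. A fuller definition elsewhere would contradict the 'fatal' label and the relatedness limit, not make them correct.

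Three stronger readings are tempting, and the documents do not support them.

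- A reader might infer that the trial's safety table, or its comparison of harms between groups, will be wrong. The article specifies neither, so the most that can be said is that events reported by these classes would be mislabelled.
- A reader might infer that deaths have no place at all. The safety list does not name death, but the abstract's word 'fatal' plausibly covers it.
- A reader might infer that the unblinded treating physiotherapists decide what is intervention-related, which would open the classification to bias. The article does not say who makes that judgement. The Blinding section keeps those therapists out of outcome evaluation, data handling and analysis, and the safety section places procedures under the monitoring team and a physician.

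**Conclusion.** The concern holds as a fault of definition. The article labels survivable serious harms 'fatal' in two places, and its serious class admits infection and vascular compromise only when they are intervention-related. If events are reported by the two stated classes, an ulcer is reported as fatal, and an unrelated infection, vascular event or hospital admission has no class.

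The size cannot be stated: there are no expected event rates, and any number put on it would be invented. The primary outcome, sample size and efficacy analysis are not affected.

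The conclusion rests on two assumptions: that events will be reported by the classes named in the abstract, and that no document outside the article overrides them. If a full protocol does hold a standard definition, the remaining task is to bring the article's wording into line with it. Either way the terms should be reconciled before safety data are coded.

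**What to change.** 1. Replace 'fatal' with 'serious' in the abstract's Methods, and remove the phrase equating serious with fatal from the safety section.
2. Define a serious event by its outcome and irrespective of cause, including death and hospitalisation, and keep the harms already listed, such as lasting nerve injury and new foot ulceration.
3. Take the relatedness condition out of the definition and record relatedness as its own field on the adverse-event form.
4. Count deaths separately from other serious events.

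The cost is a wording change in two places and an added field on the form. The one drawback is that a few more events will be reported as serious, since unrelated ones will now qualify. Nothing in the treatment schedule, the efficacy analysis or the sample size has to change.

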## Methods

### Study design

The study will be an assessor and patient-blinded Randomized Clinical Trial (RCT) at the Nurul Islam Diabetic Center in Jashore, Bangladesh. Ninety (90) patients diagnosed with DPSN by a diabetic foot surgeon and experiencing pain, burning, or tingling in the lower limbs or peripheral nerves will be randomly recruited via hospital-based simple randomization between April 2025 and August 2025. The recruited patients will be randomly allocated to either the Neurodynamic Mobilization (Experimental) (n = 45) or Sham Neurodynamic Mobilization (Control) (n = 45) groups in a 1:1 ratio using simple random sampling. The experimental group will receive Neurodynamic mobilization, and the control group will receive Sham Neurodynamic Mobilization for 12 sessions in 4 weeks; both groups will receive common foot exercises and transcutaneous electrical nerve stimulation (TENS) as a common treatment. The post-test will be taken 4 weeks after baseline assessment and recruitment, and the follow-up will be taken 12 weeks after the post-test. The follow-up assessment of the last recruited participant will end by August 2025. The study protocol will follow the Fig 1. SPIRIT (Standard Protocol Items: Recommendations for Interventional Trials) guideline of the study protocol, ensuring a clear and comprehensive study design, including participant recruitment, randomization, intervention allocation, and follow-up assessments.. The results will be reported in accordance with the CONSORT (Consolidated Standards of Reporting Trials) flow diagram (Fig 2) of participant progression, which shows the flow of participants through the enrollment, allocation, follow-up, and analysis phases of the randomized clinical trial.

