### Data analysis

All statistical analyses will be performed using appropriate statistical software (SPSS Statistics, version 23). Descriptive statistics will be used to summarize baseline characteristics, with continuous variables presented as mean ± standard deviation (SD) and categorical variables as frequencies and percentages. A p-value < 0.05 will be considered statistically significant, with a 95% confidence interval (CI). The Shapiro-Wilk test and graphical analysis will be used to assess whether the data are normally distributed. A repeated-measure ANOVA will be used to analyze group differences (intervention vs. control), changes over time, and the group-by-time interaction to assess treatment effects. Appropriate nonparametric tests, such as the Friedman test for within-group comparisons and the Mann–Whitney U test for between-group comparisons, will be employed if the assumptions required for parametric testing are not met. When appropriate, post hoc analyses will be carried out, and Type I error will be controlled using the Bonferroni correction. All randomized participants will be included in the analysis using an intention-to-treat (ITT) strategy, and missing data will be handled appropriately based on the last observation carried forward method.

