One of the key findings of this study will be the improvement in the Michigan Diabetic Neuropathy Score (MDNS) among participants in the experimental group. The reduction in MDNS scores will suggest that neurodynamic mobilization positively impacts nerve function and reduces sensory disturbances. On the other hand, improvements in the Visual Analog Scale (VAS) scores will indicate that participants experienced less pain after receiving the intervention. This will be important because chronic pain is a major concern for individuals with DPN, affecting their daily activities and quality of life [55,56]. Another significant outcome of this study will be the improvement in Neuropathy-Specific Quality of Life (Neuro-QoL) scores**.** Participants in the experimental group reported better physical function, reduced pain-related limitations, and improved overall well-being [45–50]. This suggests that neurodynamic mobilization, along with foot exercises, may enhance daily functioning and reduce the risk of further complications, such as falls and foot ulcers [11,12]. Possible explanations for these improvements are that neurodynamic mobilization promotes nerve gliding and reduces mechanical stress on nerves, which will help restore normal nerve function. The techniques used in this study will target key nerves affected in DPSN, including the sciatic, tibial, sural, and common peroneal nerves. By enhancing nerve mobility, the intervention may have improved sensory and motor function in the lower limbs [54,57,58]. The inclusion of foot exercises in both groups will have also contributed to positive outcomes. These exercises will help improve sensory input, circulation, and muscle strength, which are essential for maintaining foot health in individuals with DPSN [53,54,57,58]. The control group will also show some improvement, likely due to the benefits of foot exercises and Transcutaneous Electrical Nerve Stimulation (TENS) therapy, which is known to reduce pain and improve circulation. However, the experimental group will show greater improvements, indicating that neurodynamic mobilization provides additional benefits [41–45].

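### The serious class for nerve injury requires permanent loss, which the last visit is poorly placed to establish, and the other class does not cover sensory or motor loss, so such deficits can be misclassified or missed

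*Protocol article*

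**What the plan says.** The section on safety measures and managing adverse effects sets up two classes.

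- **Manageable events:** "Temporary increase in pain or tingling sensation and mild muscle soreness or fatigue".
- **Serious events:** these open with "severe nerve injury leading to permanent loss of sensation or motor function", followed by foot ulceration and by intervention-related complications that lead to infection or vascular compromise. The list is introduced as events considered fatal.

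The same section adds that "any adverse incidents will be documented and submitted to the ethics committee". The abstract uses the same two labels: "manageable and fatal adverse events will be documented and reported".

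The timing of the last visit is stated in two ways. Study design says "the follow-up will be taken 12 weeks after the post-test". The abstract says "A pretest will be taken at baseline, a posttest after 4 weeks, and a follow-up evaluation after 12 weeks".

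MDNS is the primary outcome and is described as three sensory tests. Its stated analysis is a comparison by group and time: "A repeated-measure ANOVA will be used to analyze group differences (intervention vs. control), changes over time, and the group-by-time interaction to assess treatment effects". Rank tests are the fallback, and missing values are filled by last observation carried forward (LOCF). The Discussion reads a fall in the score as benefit: "The reduction in MDNS scores will suggest that neurodynamic mobilization positively impacts nerve function and reduces sensory disturbances".

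**The concern.** The protocol itself names nerve injury with lost sensation or motor function as a serious harm. It then makes the serious label depend on a status for which it gives no time criterion and which a short follow-up can hardly settle. The other class has no entry for lost sensation or strength. A participant who leaves the trial with a new or worse deficit, not shown to be permanent, has no defined place in the safety table.

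Recognition may also be harder than usual. Participants already have sensory neuropathy and enter with MDNS above 6, so some may not notice further loss.

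At stake is the safety statement that will stand beside the efficacy result. A report of no serious nerve injury could reflect the definition and not what happened to participants.

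**Working it through.** **1. When the last visit falls.** Treatment lasts 4 weeks and the post-test is at week 4. By Study design, the last visit is at week 4 + 12 = week 16, which is 12 weeks after the last session. By the abstract, read from baseline, it is at week 12, which is 12 − 4 = 8 weeks after the last session. The article describes no later assessment. A deficit first found at the last visit has no second trial observation.

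**2. Deficits set against the two classes.**

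| Finding | Manageable class | Serious class |
|---|---|---|
| Transient pain, tingling, mild soreness or fatigue | yes | no |
| New or worse sensory or motor loss that resolves | not listed | no, not permanent |
| New or worse sensory or motor loss still present at the last visit | not listed | only if someone declares it permanent |
| Severe nerve injury with loss accepted as permanent | no | yes |

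The second and third rows are the gap.

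**3. The label.** Nerve injury, ulceration, infection and vascular compromise are not deaths, yet the safety section and the abstract use the word fatal for the upper class. Read literally, the abstract's commitment covers manageable and fatal events and leaves out serious non-fatal ones.

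**4. What small numbers mean here.** Each arm has 45 participants.

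- One case moved between classes changes the arm's rate by 1/45 = 2.2 percentage points.
- With 0 events in 45, the one-sided 95% upper bound is 1 − 0.05^(1/45) = 6.4%.
- The chance of at least one event in 45, 1 − (1 − p)^45, is 36%, 60% and 90% for true rates p of 1%, 2% and 5%.

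A zero count is weak evidence even with a sound definition. If cases can fall between classes, it is weaker.

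**5. Could the MDNS comparison reveal it instead?** The plan's own figure comes first. With d = 0.62, two-sided alpha 0.05 (the plan does not state sidedness) and power 0.80, a t-based calculation gives 41.8, so 42 per group, as stated.

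The documents give no SD for MDNS. As an illustration only, assume an SD of 6 points, and that 3 of 45 active participants worsen by 10 points instead of improving by the planned effect.

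- Planned effect: 0.62 × 6 = 3.72 points.
- Shift in arm mean: 3 × (10 + 3.72)/45 = 0.91 points.
- Remaining difference: 3.72 − 0.91 = 2.81 points, still in favour of treatment.
- Active-arm variance: 36 + (3/45)(42/45)(13.72²) = 47.7, so SD 6.9. Pooled SD: √((47.7 + 36)/2) = 6.47.
- Standardised difference: 2.81/6.47 = 0.43. With 45 per arm, power falls from 0.83 to 0.53.

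For assumed SDs of 4 and 8, the remaining differences are 1.65 and 3.96 points (d = 0.36 and 0.47). The mean stays favourable but the result is clearly weakened. The group comparison neither conceals such harm completely nor identifies it.

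**6. Effect of LOCF.** A participant who worsens and stops attending before the post-test has the baseline value carried forward. The recorded change is baseline − baseline = 0, so the participant counts as unchanged.

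**The case against.** The strongest reply is that nothing goes unreported, because the safety section sends every adverse incident to the ethics committee whatever its class. This stands. A reader might infer that nerve injury could be left out of the reports altogether, and the documents do not support that. The rule does not, however, say how such an incident is classed, and it works only once someone has recognised one.

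Second, a qualified physician supervises the procedures and may judge prognosis without waiting for a visit. This is fair, and the reason to say poorly placed and not impossible. It does not give non-permanent loss a class.

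Third, detection does not rest on self-report alone: a blinded assessor examines every participant who attends, and Neuro-QoL also asks about foot sensation and balance. That stands too. MDNS is therefore not the only measure touching this harm, and as described it has no motor test and could not show motor loss. What the article lacks is a link from such a finding to the adverse-event record.

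Fourth, a safety analysis of MDNS may sit in a full protocol or analysis plan that is not shown. Its absence from a condensed article is not a defect and is not claimed as one. Comparing a primary outcome between groups is also not an error.

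Two further inferences go too far. The documents do not rank nerve injury as the main harm of the treatment; they list it beside the others. Nor can it be said that a few harmed participants would leave no trace in the efficacy result, since the illustration shows a marked loss of power.

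**Conclusion.** The point holds for the definitions. The two adverse-event classes leave new or worsened sensory or motor loss without a class unless it is called permanent, follow-up of about 8 to 12 weeks after the last session is a weak basis for that call, and the fatal label is wrong for the events listed. The consequence is possible misclassification as non-serious, or non-recognition, and so an understated count of serious nerve injury.

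The size cannot be derived from the documents. At 45 per arm, each case affected is worth 2.2 percentage points. The MDNS figures rest on an assumed SD, an assumed number harmed and an assumed worsening. They show only that a favourable mean and a few harmed participants can coexist. That follow-up is too short to establish permanence is a judgement, because the documents set no time criterion. The change is worth making because it costs so little.

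**What to change.** 1. Reconcile the abstract, Study design and the safety section, including the timing of the last visit, so that the reporting classes cover every new or worsened sensory or motor deficit.
2. Base the serious class for nerve injury on a status that can be observed within the trial's follow-up, for example unresolved at the participant's last visit. The final wording is for the investigators.
3. Remove the fatal label from events that are not deaths, in both the safety section and the abstract.
4. As support, report by arm the number of participants whose observed MDNS, without LOCF, is worse than baseline at the post-test and at follow-up, and check these participants against the adverse-event record. Motor loss can come only from that record, since no scheduled measure as described tests it.

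The cost is a few reworded sentences and one table from data already collected, with no new visit or test. The downside is that some worsening will be measurement noise or disease progression. The sham arm helps to gauge how much.
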